### Outcomes

We will assess physical growth with 1) anthropometry and 2) body composition analysis. At study start and end points, we will weigh infants in duplicate on a calibrated portable digital scale; if the infant is not stable enough to be weighed on a portable scale, we will use the built-in isolette scale. Body length will be measured in duplicate with a recumbent length board and head circumference with a non-stretchable tape and both recorded to 0.1 cm. One of two registered neonatal dietitians will perform all anthropometric measurements, assisted by a trained research assistant and with other clinical assistance (e.g. bedside nurse, respiratory therapist) as indicated. Interrater reliability between the 2 dietitians will be assessed at baseline and quarterly throughout the study period. We will use an infant air displacement plethysmography system (PEA POD, Cosmed, Concord CA) to measure infant body volume and mass and estimate fat mass and fat free mass with a 2-compartment model [26]. Infants will undergo body composition assessment as soon as possible upon study start, with timing based on the ability to remain off respiratory support during the assessment, and again at study end point.

We will assess structural brain development with MRI. Infants will be scanned without sedation at term equivalent age (38–41 weeks’ postmenstrual age, PMA) using a “feed and wrap” method [27]. We will use a 3 Tesla Prisma system (Siemens) equipped with a 16-channel pediatric head coil. To derive the primary volumetric outcomes (total brain volume, cerebellar volume), we will use an automated segmentation method, MANTiS [28]. A secondary MRI outcome will be fractional anisotropy in the posterior limb of the internal capsule (PLIC), a measure of white matter microstructure. We will manually delineate the PLIC using region-of-interest based analysis [29].

To assess neurodevelopment at 2 years’ corrected age, we will use the Bayley Scales of Infant and Toddler Development, 4th edition [30]. Primary outcomes will include the cognitive and motor scores (continuous). Secondary outcomes will include cognitive and motor delay (scores < 85) and the language score (continuous and < 85). We will assess spatial working memory with the “Spin the Pots” task, [31] behavioral inhibition with the “Mommies and Babies” task, [32] and executive function and behavioral difficulties using valid parent questionnaires [33, 34]. At 2 years, we will reassess anthropometry using similar methods to those described previously, and assess blood pressure with an automated oscillometric device.

To promote cohort retention and collect interim data on infant development, we will administer maternal questionnaires at 4 and 12 months’ corrected age, including the Baby Pediatric Symptom Checklist, Motor and Social Development Scale, [35] Ages and Stages, [36] and Infant Toddler Quality of Life scale [37].

### Participant timeline

The timeline of enrollment, interventions, and assessments are shown in Fig. 2.

**Fig. 2 Fig2:**
[figure not shown]
Nourish study timeline of enrollment, interventions, and assessment. The study diet will start the first weekday that the infant reaches a full volume, fortified enteral diet (≥140 mL/kg/day human milk). The study diet will end at 36 weeks’ postmenstrual age (PMA). Anthro is anthropometry (weight, length, head circumference). BC is body composition assessed with air displacement plethysmography. MRI will be obtained at 38–41 weeks’ PMA. Bayley Scales of Infant and Toddler Development, 4th edition will be used. Spatial working memory will be assessed with the “Spin the Pots” task, behavioral inhibition with the “Mommies and Babies” task, and executive function and behavioral difficulties with parent questionnaires (Behavioral Rating Inventory of Executive Function – Preschool Version; and Infant-Toddler Symptom Checklist—Long Version). Ages in the follow-up phase are corrected ages (age corrected for preterm birth)

### Sample size

The planned sample size is 130 infants (65 per study group). Accounting for expected attrition (5% by NICU discharge due to death or unexpected transfer) and an additional 5% loss due to uncorrectable motion artifact for MRI outcomes, we expect to be able to detect a moderate effect of the intervention on primary outcomes (0.49 z-scores in weight, 0.24 z-scores in fat free mass, 24 cc total brain volume) at α = 0.05 and power 0.8. Accounting for 10% further attrition to 2 years’ corrected age, we have adequate power to detect an 8.1-point difference between groups on the Bayley cognitive scale.

### Assignment of interventions

We will use permuted block randomization and assign participants 1:1 to the standard of care diet (control) or individually fortified diet (intervention). Twins will be randomized individually. The study biostatistician will generate the allocation sequence and place the assignments in envelopes, to be opened by the research assistants on the study start date.

### Blinding

Parents, clinical staff, and all study staff apart from the research assistants who prepare the study diet will be blinded to the study group. Blinding will be facilitated by the use of amber enteral feeding tubes to hide the appearance of the milk. Unblinding will be permitted if an error in milk preparation is identified, if a participant experiences growth faltering despite all strategies outlined in the protocol, or if unexpected safety concerns arise that require unblinding.

### Data collection and management

Most study data will be stored in Research Electronic Data Capture (REDCap), a secure, HIPAA compliant application. Maternal questionnaires will be both administered and stored within REDCap. Milk analysis and PEAPOD data will be downloaded directly from the devices onto flash drives and transferred to a secure shared server. MRI files will be transferred directly from the scanner to a research server.

### Collection and storage of biological specimens for future use

We will collect 2 mL of unfortified milk and 1 mL of fortified milk each time milk is prepared for the study diet and store it at − 80 °C.

### Statistical methods

Our overall analytic strategy compares pre-specified primary and secondary outcomes between control and intervention groups. We will follow the intention-to-treat principle and analyze data for all enrolled participants. We will use multiple imputation to address missing data due to death or loss to follow-up. Results will be expressed as mean or median differences with 95% confidence intervals. We will use mixed linear models adjusted for intrafamilial clustering due to multiple births, along with control for baseline covariates, as needed, to minimize effects of between-group differences in baseline factors due to chance. We will examine intervention effects in the complete cohort and use stratification approaches to explore the effects of variables specified a priori including sex, fetal growth status (SGA vs. non-SGA), and gestational age (24–27 weeks vs. 28–30 weeks).

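### Covariate adjustment in the primary models is tied to chance baseline imbalance, which leaves the model open once baseline data are seen and gives up precision from prognostic values already collected

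*Protocol article*

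**What the plan says.** Statistical methods gives the model and the adjustment rule in one sentence. The model: "We will use mixed linear models adjusted for intrafamilial clustering due to multiple births". The rule: "along with control for baseline covariates, as needed, to minimize effects of between-group differences in baseline factors due to chance". No covariate is named, and nothing says when adjustment counts as needed. The next sentence does name variables in advance, but only for subgroup work: the plan will "use stratification approaches to explore the effects of variables specified a priori including sex, fetal growth status" and gestational age group.

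Outcomes describes what is available at the start: "At study start and end points, we will weigh infants in duplicate on a calibrated portable digital scale". Length and head circumference are described in the same set of measurements, and the legend of Fig. 2 defines anthropometry as weight, length and head circumference. Body composition is timed differently: "Infants will undergo body composition assessment as soon as possible upon study start", depending on whether the infant can remain off respiratory support.

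Assignment of interventions describes permuted blocks with 1:1 allocation and states no stratification factor.

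**The concern.** Under randomisation, the standard error already allows for chance imbalance. Adjustment helps when a covariate predicts the outcome, because it removes explained variation. A rule driven by imbalance selects on the wrong property: it drops a strong predictor that happens to balance and admits a weak one that does not.

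Two things are at stake. First, the primary model is not fixed before baseline data are seen. There are six primary measures (length and lean mass in the abstract, total brain and cerebellar volume and Bayley cognitive and motor scores in Outcomes), and the need for adjustment could be judged separately for each. Second, precision is lost in a trial whose Discussion already names sample size as a limitation.

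**Working it through.** **Inputs from the document.** 65 infants per group; attrition of "5% by NICU discharge due to death or unexpected transfer"; α = 0.05 and power 0.8 (Sample size). Sidedness is not stated, so two-sided is assumed.

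**Inputs assumed.** The correlation r between study-start and 36-week length is not given; 0.3 to 0.7 is used. Outcomes are in SD units.

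**Step 1: the plan's own figure.** Detectable difference = (1.960 + 0.842) × SD × √(2/n).
- n = 65, SD = 1: 2.802 × √(2/65) = 0.491.
- n = 65 × 0.95 = 61.75, SD = 1: 2.802 × √(2/61.75) = 0.504.

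The plan states 0.49 z-scores for weight. That matches SD 1 with no attrition, or SD 0.49/0.504 = 0.97 after 5% attrition. The document gives no SDs, so the figure cannot be strictly reproduced, and it gives no detectable difference for length. The unadjusted reference here is 0.504 SD.

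**Step 2: adjustment for study-start length.** The residual SD is multiplied by √(1 − r²), and so is the detectable difference. Power is for a true difference of 0.504 SD.

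| r | √(1 − r²) | Detectable difference (SD) | Power |
|---|---|---|---|
| 0 | 1 | 0.504 | 0.80 |
| 0.3 | 0.954 | 0.48 | 0.84 |
| 0.5 | 0.866 | 0.44 | 0.90 |
| 0.7 | 0.714 | 0.36 | 0.97 |

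**Step 3: the right comparator.** Step 2 compares full adjustment with none, but the plan allows some adjustment. A simulation therefore compared the rules directly: 62 per arm, four independent baseline covariates (one with correlation r to the outcome, three with 0.15), 8,000 trials per setting, no twin clustering. In the trigger rules a covariate enters only if its baseline comparison gives p below the threshold. The pre-specified model contains the strong covariate only.

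Power at a true difference of 0.504 SD:

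| Rule | r = 0.5 | r = 0.7 |
|---|---|---|
| Unadjusted | 0.80 | 0.79 |
| Adjust if imbalance p < 0.05 | 0.81 | 0.81 |
| Adjust if imbalance p < 0.2 | 0.83 | 0.86 |
| Pre-specified | 0.89 | 0.97 |

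Type I error with no true difference:

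| Rule | r = 0.5 | r = 0.7 |
|---|---|---|
| Unadjusted | 0.049 | 0.054 |
| Adjust if imbalance p < 0.05 | 0.039 | 0.036 |
| Adjust if imbalance p < 0.2 | 0.034 | 0.026 |
| Pre-specified | 0.048 | 0.049 |
| Most favourable of five covariate sets | 0.090 | 0.106 |

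The last row picks the smallest p-value among five models: no covariates, the strong one, one weak one, those two together, and all four. It represents a choice made with the outcome in view. The simulation was not run at r = 0.3, where all the differences in power would be smaller.

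**The case against.** The strongest reply is that covariate lists belong in the SAP, which is not shown. That is right about the list, and its absence is not criticised here. But the article goes further than silence: it states the principle of selection, and an SAP that follows it would carry the principle over.

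The second reply is that the gain is narrow and rests on an unknown correlation. This stands. MRI and Bayley outcomes have no study-start value, and for fat-free mass the safe covariates are weight and length rather than the same measure, so the calculation applies directly to length only. The 0.504 SD starting point also holds only at 5% attrition; Sample size adds 5% loss for MRI and 10% further attrition to 2 years.

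A reader might infer that the rule inflates type I error. Applied mechanically, it does the opposite: error was 0.026 to 0.039. Inflation needs outcome-driven choice, which the article neither describes nor rules out.

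A reader might also infer that the fat-free-mass effect will be biased towards zero, because the first PEA POD assessment can fall after the diet begins. The article does not propose that measurement as a covariate and does not say how late it falls. This is a caution for the SAP, not an error in the plan.

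**Conclusion.** The point holds as a criticism of the stated selection principle. Adjusting because of chance imbalance leaves the primary models open after baseline data are seen and recovers little of the precision that prognostic covariates offer.

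The size is illustrative and for length only. Full adjustment would bring the detectable difference from about 0.50 SD to 0.48 SD at r = 0.3 and to 0.36 SD at r = 0.7. Against the rule as written, read as a mechanical trigger, the loss at r = 0.5 is about 6 to 8 percentage points of power (0.81 to 0.83 against 0.89). The documents do not support carrying these figures over to the brain or Bayley outcomes, where the gain depends on how well gestational age, sex and any other chosen covariate predict the outcome.

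**What to change.** Remove the *as needed* condition and the reference to chance differences. State that every primary analysis adjusts, regardless of observed imbalance, for covariates fixed in advance:

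- **All primary outcomes:** gestational age (continuous) and sex.
- **Length:** also study-start length.
- **Fat-free mass:** also study-start weight and length.
- **MRI and Bayley outcomes:** any further covariate, for example birth-weight or study-start head-circumference z-score, only if named before outcomes are examined.

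Add a note that the first PEA POD value is not used as a baseline covariate unless it was taken before the first study feed.

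The cost is wording in the protocol and SAP. Gestational age and birth weight are needed for eligibility, sex is already an analysis variable, and anthropometry is already taken at study start.

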## Methods / design

### Setting and eligibility criteria

This randomized clinical trial will take place at Brigham and Women’s Hospital, an academic Level III NICU in Boston, MA. Inclusion criteria are: 1) singleton or twin infant with gestational age at birth 24 0/7 to 30 6/7 weeks; 2) chronologic age < 21 days; and 3) mother providing milk, with clinical consent given to use pasteurized donor human milk if maternal milk is in short supply or unavailable. Exclusion criteria include: 1) major congenital anomaly; 2) birth weight < 3rd percentile [23]; 3) necrotizing enterocolitis or other clinically significant gastrointestinal pathology; 4) clinically significant renal or hepatic dysfunction or inborn error of metabolism; 5) fluid restriction < 140 mL/kg/day anticipated for 3 or more days; 6) grade 3 or 4 intraventricular hemorrhage detected prior to enrollment; and 7) anticipated transfer < 36 weeks’ postmenstrual age or expected death.

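### Subgroup effects are to be explored by stratification, which does not itself estimate whether the effect differs between strata, and the SGA stratum, cut off at the 3rd percentile, will be very small

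*Protocol article*

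**What the plan says.** Under Statistical methods, the protocol article examines the effect in the whole cohort and will then "use stratification approaches to explore the effects of variables specified a priori including sex, fetal growth status (SGA vs. non-SGA" split); the third variable is gestational age, 24–27 against 28–30 weeks. The same section says that results are given as differences with 95% confidence intervals, from mixed linear models that allow for clustering of siblings. It names no interaction term.

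Setting and eligibility criteria excludes infants with "birth weight < 3rd percentile". SGA has no stated cut-off (Abbreviations only spells it out), and no expected number of SGA infants is given.

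On size, Sample size says "The planned sample size is 130 infants (65 per study group"), "at α = 0.05 and power 0.8".

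**The concern.** There are two linked problems.

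- **Method.** The question behind each modifier is whether the treatment effect differs between its levels. Separate stratum estimates leave the reader to judge that by eye. A common way of doing so, noting that one stratum reaches significance and the other does not, can suggest a difference where the effect is the same in both. Cutting gestational age into two bands also discards information.
- **The SGA stratum.** The eligibility rule removes the most growth-restricted infants, so a stratum labelled SGA would not represent SGA infants in general. What is left is also too few for a useful within-stratum estimate.

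At stake is the reading of the subgroup results. The primary comparison does not depend on it.

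**Working it through.** **Inputs from the protocol article.** 65 infants per arm; alpha 0.05 and power 0.8 (sidedness is not stated, so two-sided is assumed); loss of "5% by NICU discharge due to death or unexpected transfer", giving 65 × 0.95 = 61.75 per arm analysed; exclusion below the 3rd percentile.

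**Assumptions.** SGA means below the 10th percentile. The SGA share is varied. Effects are in SD units, and twin clustering is ignored.

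**1. The plan's own figures.** The article gives no subgroup size or subgroup power to reproduce. Its overall detectable differences ("0.49 z-scores in weight, 0.24 z-scores in fat free mass, 24 cc total brain volume", and 8.1 Bayley points) carry no SDs.
- With an assumed SD of 1, 0.49 has power 0.798 at 65 per arm and 0.777 at 61.75.
- With an assumed SD of 15, 8.1 points has power of about 0.79 to 0.81 at 52 to 55.6 per arm. These are 65 × 0.80, with all three stated losses added, and 65 × 0.95 × 0.90.

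Both fit a trial that can detect about half an SD. By the normal approximation:

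(1.960 + 0.842) × √(2/61.75) = 0.504 SD. This is called the design effect below.

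**2. Size of the SGA stratum.** If eligible infants follow the reference distribution, the share is (0.10 − 0.03)/(1 − 0.03) = 0.072, and 130 × 0.072 = 9.4 infants (95% binomial range 4 to 16). Detectable differences use a t-test with 5% loss.

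| SGA share | Infants of 130 | Per arm | Detectable difference |
|---|---|---|---|
| 7.2% | 9.4 | 4.7 | 2.2 SD |
| 10% | 13 | 6.5 | 1.8 SD |
| 15% | 19.5 | 9.8 | 1.4 SD |
| 20% | 26 | 13 | 1.2 SD |

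Even at a 20% share, the stratum can detect only a difference more than twice the overall 0.5 SD.

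**3. Disagreement between strata when the effect is the same in both.** Suppose a reader compares significance across two strata with powers p₁ and p₂. The chance that they disagree is p₁(1 − p₂) + p₂(1 − p₁). For equal strata (30.875 per arm each) at the design effect, the standardised effect is 0.504/√(2/30.875) = 1.98. Power is therefore 0.508 in each, and disagreement is 2 × 0.508 × 0.492 = 0.50.

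| Common true effect | Equal strata | 7.2% SGA stratum |
|---|---|---|
| None | 9.5% | 9.5% |
| Half the design effect | 28% | 30% |
| Design effect | 50% | 71% |
| 1.5 × design effect | 26% | 79% |

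**4. What an interaction test gives.** The false-positive rate is 5% per modifier. The standard error is the root of the summed stratum variances.
- Equal strata: √(2 × 2/30.875) = 0.360, so the detectable interaction is 2.802 × 0.360 = 1.01 SD. Power for an interaction as large as the design effect is Φ(0.504/0.360 − 1.96) = 0.29.
- 7.2% SGA split: the detectable interaction is 1.95 SD and the power is 0.11.

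The gain from continuous birth-weight z-score or gestational age cannot be computed, because the article gives no distribution or slope.

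**The case against.** The strongest reply is that the article describes exploration of pre-specified variables, reported with confidence intervals, and that a condensed article may leave the form of an exploratory subgroup test to the full protocol or analysis plan. That stands in part: the missing interaction test is not in itself an error. But the article does name a method, stratification, and a better one is available within the model it already plans.

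Two stronger readings are tempting, and the documents do not support them.

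- **That the exclusion nearly empties the SGA stratum.** With an SGA share of 10% and no exclusion, 130 infants would include 13 SGA infants; with it, about 9.4. The loss is (13 − 9.4)/13, about 28%. The stratum is small mainly because the trial is small, and the SGA cut-off and share are not stated. The Discussion concedes that the sample size may miss small effects, though it does not mention subgroups.
- **That the plan will produce false subgroup differences about half the time.** The 50% figure is the maximum for equal strata, reached when the common effect is about the design effect. It also needs a comparison of significance between strata, which the article nowhere says it will make.

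It is also fair to say that interaction terms do not make these subgroups informative.

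**Conclusion.** The point holds as a modest one. Stratification does not itself estimate effect modification for any of the three variables. If SGA means below the 10th percentile, that stratum is confined to the 3rd to 10th percentile band. It would hold about 9 infants if the cohort follows the reference, or 13 to 26 at shares of 10 to 20%. Its detectable difference is about 2.2 SD, or 1.8 to 1.2 SD at the larger shares, against about 0.5 SD for the whole trial. The conclusion that the stratum is too small does not depend on which of these shares applies.

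The disagreement rates (50%, 28% and 9.5% for equal strata at the design effect, half of it, and no effect) describe a risk in how stratum results may be read, not a procedure in the plan. The primary analysis, the sample size and the main conclusion are unaffected.

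**What to change.** - In the planned mixed model, add a treatment-by-modifier term for each variable and report its estimate with a 95% confidence interval. Use birth-weight z-score and gestational age in weeks as continuous modifiers, and sex as binary. Stratum estimates may be shown beside these.
- State the SGA cut-off and reference, and say that the stratum is truncated at the 3rd percentile by the eligibility criteria. Show the SGA stratum descriptively only.
- Keep the exploratory label, and say that significance will not be compared between strata.

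The cost is analysis wording and a few extra model terms, with no new data or participants. There are two downsides. A continuous modifier needs an assumed functional form, usually linear. Power for interactions also stays low: about 29% for equal strata and 11% for the 7.2% SGA split, when the interaction is as large as the design effect.

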## Discussion

Here, we describe the protocol for a randomized, controlled trial of individually targeted human milk fortification during the NICU hospitalization for preterm infants born at 24 to 30 completed weeks’ gestation. We will measure the effectiveness of this intervention in terms of 1) increasing physical growth and optimizing body composition during the NICU hospitalization; 2) improving structural brain development by term equivalent age; and 3) improving neurodevelopmental outcomes at 2 years’ corrected age.

Our protocol has several strengths. One is the integration of our intervention into the NICU workflow. Another is our combination of standard and innovative outcome measures. For example, we will assess not just standard anthropometry but also infant body composition, including fat-free mass which indexes muscle and organ growth. Brain MRI at term equivalent age will enable us to detect short-term effects of the nutritional intervention on brain size and microstructure. At 2 years’ corrected age, measures of working memory and behavioral inhibition, which reflect emerging executive function, as well as measures of sustained attention and self-regulation will complement the standard Bayley scales. Another strength is the “triple blinding” of parents, clinicians, and study staff to minimize biases that could affect participant allocation, assessment, and/or adherence to the intervention. Limitations include the single-center design, which may reduce generalizability, and the sample size, which may preclude the detection of small but clinically important effects. Additionally, the intervention is labor intensive, with future work needed to optimize for scalability.

In conclusion, we have designed a randomized controlled trial to test the effectiveness of individually targeted human milk fortification during the NICU hospitalization. This nutritional intervention during a critical period in preterm infant brain development has the potential to improve both short and long-term outcomes for very preterm infants.

